### Sample size

On the basis of the results observed in the publication by Lammers et al. [13], 50% of adolescents who have had at least one binge-drinking episode in the last month are expected in the control arm while 35% are expected in the intervention group. With an alpha risk of 0.05 and a potency of 80%, the sample size should be 170 patients/group, or 340 patients in all. As the expected proportion of “at-risk” subjects (who will be randomised) is of the order of 1 in 2 among the adolescents included, an initial number of 700 adolescents is planned to be included (including a proportion of subjects not evaluated for the main criterion).

Thirty-three centres will be included, distributed across 8 hospital structures and the general medicine network, corresponding to less than one patient/month per investigator.

The duration of the inclusion period will be 36 months, the duration of participation for each patient will be 15 months, and the total duration of the study will be 51 months.

### Statistical analysis

The prevalence rates of adolescents who have experienced at least one binge drinking episode (more than 5 standard units) in the last month (measured at 6 months after intervention -main criterion) will be compared using logistic regression with adjustment for stratification factors between the two groups (intervention and control). As an exploratory measure, the interaction between the intervention and the type of risk profile will be tested, looking for possible heterogeneity of effect of the intervention according to the type of profile. In the case of a significant interaction, results by type of profile can be provided on an exploratory basis.

The binary secondary judgement criteria (pass/fail) will be analysed in the same way as the main criterion.

Quantitative judgement criteria will be analysed using a linear model with adjustment for stratification factors. The interaction term between intervention and profile type can be tested in the same way as for the main criterion.

Quantitative measurements repeated during monitoring will be modelled using a mixed linear model to take intra-subject correlation into account.

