### Intervention

The *Preventure* program consists of two 90-min sessions with delivered to small groups of students (i.e., approximately 4–6 students per group), led by a trained facilitator. In 2020, this program was adapted for online delivery via videoconferencing platforms and can now be accessed by adolescents on smartphones, tablets or computers. This online program enables wider access to the intervention for adolescents, whether they live in rural, semi-urban or urban areas .

Supported by real-life scenarios, and based on CBT and MI techniques, the sessions will incorporate:

1) Psychoeducation about the targeted personality trait (i.e., impulsivity, sensation seeking, anxiety sensitivity, hopelessness/negative thinking) and associated maladaptive coping behaviours.

2) The development of an individualized model of the physiological, cognitive and behavioural components of typical responses.

3) Motivational enhancement, goal setting and application of cognitive-behavioural skills to tackle problematic reactions and behaviour.

Each adolescent will receive the intervention corresponding to their predominant personality trait.

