### Randomisation

Adolescents will be randomised [1], and the randomisation will be stratified according to the predominant type of risk-prone personality trait (4 types) presented by the adolescents and according to recruitment conditions (school care vs. primary or specialised adolescent care). The control group will receive the usual routine follow-up (individual consultations in primary care / or in adolescent care facilities/ adolescent addictive disorder consultations) and assessments.; The intervention group will receive the usual follow-up, assessments plus the Preventure program tailored to one personality type among the 4 risk-related personality traits.

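### Preventure is delivered in groups in one arm only, but neither the analysis models nor the 170 per arm allow for correlation within those groups

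*Protocol article*

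**What the plan says.** The Intervention section of the protocol article says the programme is "delivered to small groups of students (i.e., approximately 4–6 students per group), led by a trained facilitator", over two 90-minute sessions. It adds: "Each adolescent will receive the intervention corresponding to their predominant personality trait". Group delivery applies to the intervention arm only. Under Randomisation, "The control group will receive the usual routine follow-up (individual consultations in primary care" and other adolescent care settings. Adolescents are randomised individually, and "the randomisation will be stratified according to the predominant type of risk-prone personality trait (4 types) presented by the adolescents", with recruitment condition as the second factor.

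Under Statistical analysis, the primary rates "will be compared using logistic regression with adjustment for stratification factors between the two groups (intervention and control"). Binary secondary criteria follow the same method, and quantitative ones use a linear model with the same adjustment. The only correlation the section addresses is within a person: repeated quantitative measurements "will be modelled using a mixed linear model to take intra-subject correlation into account".

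The Sample size section expects 50% with a binge-drinking episode in the control arm and 35% in the intervention arm, with alpha 0.05 and 80% power, and arrives at 170 per group. It mentions neither an ICC nor a design effect.

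**The concern.** This is a partially nested design: individuals are randomised, but only one arm is then treated in groups. Members of a delivery group share a facilitator, the discussion and the goal-setting work. The outcome is drinking, which the Background section itself links to social influences. Outcomes may therefore be correlated within groups in the intervention arm and independent in the control arm.

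Adjusting for the stratification factors does not deal with this. Trait and recruitment condition identify neither the delivery group nor the facilitator; they remove only the correlation that comes from sharing a trait or a recruitment route.

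If the within-group ICC is positive, the stated model understates the variance of the intervention arm. Confidence intervals are then too narrow, the test rejects too often, and a test that is valid has less power than planned. Because the secondary models have the same structure, the gap runs through the whole efficacy analysis.

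**Working it through.** **Inputs from the article.** Group size m about 4–6 (Intervention); 50% against 35%, alpha 0.05, power 80%, 170 per arm (Sample size). At 170 per arm this means about 170/6 ≈ 28 to 170/4 ≈ 43 groups. The article does not state sidedness.

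**Input assumed.** The ICC, taken over 0 to 0.10 because the article gives none.

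**Reproducing the plan's figure.** With the pooled-variance formula and a two-sided test, the mean rate is 0.425 and

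n = [1.96·√(2·0.425·0.575) + 0.8416·√(0.50·0.50 + 0.35·0.65)]² / 0.15² = (1.370 + 0.582)² / 0.0225 ≈ 169.3, so 170 per arm.

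Power at 170 is 80.2%. A one-sided test would need 134, so the figure is two-sided, and it contains no design effect.

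**Effect of clustering in one arm.**

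- Design effect in the intervention arm: DE = 1 + (m − 1)·ICC.
- True over naive standard error under the null: √((1 + DE)/2).
- Actual two-sided alpha of the unclustered test: 2·[1 − Φ(1.96 / √((1 + DE)/2))].
- Power of a valid test: Φ[(0.15 − 1.96·SE₀)/SE₁], with SE₀ = √(0.425·0.575·(1 + DE)/170) and SE₁ = √((0.25 + DE·0.2275)/170).

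Worked case, m = 5 and ICC 0.05: DE = 1.20; standard-error ratio √1.10 = 1.049; 1.96/1.049 = 1.869, so alpha = 6.2%. SE₀ = 0.0562 and SE₁ = 0.0555, so power = Φ(0.717) = 76.3%.

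Results for m = 4 / 5 / 6:

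| ICC | DE | SE ratio | Two-sided alpha, % | Power of valid test at 170, % | Evaluable per arm for 80% |
|---|---|---|---|---|---|
| 0 | 1 / 1 / 1 | 1 / 1 / 1 | 5.0 / 5.0 / 5.0 | 80.2 / 80.2 / 80.2 | 170 / 170 / 170 |
| 0.01 | 1.03 / 1.04 / 1.05 | 1.008 / 1.010 / 1.012 | 5.2 / 5.2 / 5.3 | 79.6 / 79.4 / 79.2 | 172 / 173 / 174 |
| 0.05 | 1.15 / 1.20 / 1.25 | 1.037 / 1.049 / 1.061 | 5.9 / 6.2 / 6.5 | 77.3 / 76.3 / 75.4 | 182 / 187 / 191 |
| 0.10 | 1.30 / 1.40 / 1.50 | 1.072 / 1.095 / 1.118 | 6.8 / 7.4 / 8.0 | 74.5 / 72.7 / 70.9 | 195 / 203 / 212 |

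**Simulation check.** Beta-binomial groups in the intervention arm, independent controls, 50% in both arms, an unadjusted Wald test of the log odds ratio, 400,000 runs per setting. Rejection rates were 4.5–4.7% at ICC 0, 4.7–5.0% at 0.01, 5.6–6.2% at 0.05 and 6.5–7.7% at 0.10. They lie a little below the formula because the Wald test itself runs slightly under 5% at this size.

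**The case against.** The main objection is that everything turns on an ICC that the article does not give. That stands. At ICC 0 there is no inflation, and at 0.01 the simulated test stays at or below 5%.

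A reader might infer that the type I error is certainly above 5%, or that a null programme would be declared effective more than 5% of the time. The article supports neither reading:

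- The rates above are two-sided. About half of the rejections point towards harm, so at ICC 0.05–0.10 a false declaration of benefit has a probability of about 3–4%, against a nominal 2.5%.
- If the programme affects nobody, individual randomisation protects the test, however adolescents are later grouped. Inflation requires groups that shift outcomes in different directions around a zero average.

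There are also reasons to expect a small ICC. Contact is two sessions, possibly by videoconference, and the primary outcome is drinking in the last month, assessed six months later. The article does not say that group members know each other. If the 170 intervention adolescents were spread evenly over 36 months and four traits, about 170/(36·4) ≈ 1.2 per trait per month would arrive, so real groups could be smaller than 4–6. These points bear on the size of the effect and do not remove it.

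Finally, the full protocol and SAP are not shown and may already handle this; a robust variance is compatible with the named model. But the article does fix the models, addresses correlation explicitly within subjects only, and sizes the trial without a design effect. Followed as written, it leaves the gap open.

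**Conclusion.** The point holds in conditional form. The stated models and sample size treat adolescents who share a delivery group as independent. If the within-group ICC is positive, precision is overstated: standard errors are too small by a factor of about 1.01 at ICC 0.01, 1.04–1.06 at 0.05 and 1.07–1.12 at 0.10, with the error rates and power losses tabulated above. These figures assume equal groups of 4–6, 170 evaluable adolescents per arm, every intervention adolescent in a group, and clustering by group only; any further correlation from a facilitator running several groups is not included. The effect is modest and disappears at ICC 0, so this is something to fix rather than a flaw that invalidates the trial.

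**What to change.** - Record a delivery-group identifier and a facilitator identifier for each intervention adolescent during the trial, if this is not already done.
- Keep the logistic regression adjusted for stratification factors, and base inference on cluster-robust standard errors by delivery group with a small-sample correction. Treat each control, and each intervention adolescent who never joins a group, as a cluster of one.
- Alternatively, add a random group intercept in the intervention arm only, stating that its odds ratio is conditional on group.
- Do the same for the secondary models; in the repeated-measures mixed model, group sits above subject.
- Restate power at 170 per arm over an assumed ICC range, rather than enrolling more.

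The cost is two data fields, analysis wording and a slightly wider confidence interval. The random-intercept version may be unstable with about 28–43 small groups and a binary outcome, which favours the robust-variance version. Randomisation and treatment do not change. If the full protocol or SAP already contains these provisions, confirming that is enough.

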### Inclusion criteria

Adolescents aged 14 to 17 years, seeking treatment in one of the participating centres in primary care, or adolescent care facilities (general or addictive disorder consultations for adolescents) or identified by a school doctor or nurse, who have already experienced alcohol (at least 1 standard unit of alcohol lifetime), will be included in the study, after written and informed consent from the parents and the adolescents. They are required to have Internet access, access to a smartphone, tablet or computer.

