### Study design

This is a prospective, randomized, controlled, stratified, multicentre, open-label study aiming to evaluate the superiority of the *Preventure* program on the reduction of binge drinking episodes, over usual routine follow-up care forming the control group (individual follow-up consultations in primary care/or in adolescent care facilities/ adolescent addictive disorder consultations). It concerns a population of adolescents aged 14–17 having experimented with alcohol consumption.

The study design is presented in Fig. 1.

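### Baseline drinking is not among the covariates named for the primary logistic model or the linear models: valid as planned, but likely forgoing power

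*Protocol article*

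**What the plan says.** The Statistical analysis section compares the arms on past-month binge drinking at 6 months by logistic regression, adjusting for the factors used to stratify randomisation. The Randomisation section defines these as predominant risk trait (four levels) and recruitment route (school care against primary or specialised adolescent care). No other covariate is named.

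The same adjustment set carries over to other outcomes: "The binary secondary judgement criteria (pass/fail) will be analysed in the same way as the main criterion", and "Quantitative judgement criteria will be analysed using a linear model with adjustment for stratification factors". Repeated quantitative measurements get a mixed linear model whose covariates are not listed.

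On the range of drinking at entry, the Inclusion criteria ask for adolescents "who have already experienced alcohol (at least 1 standard unit of alcohol lifetime"). The Non-inclusion criteria remove moderate-to-severe substance use disorders other than tobacco. Past-month binge drinking is not an exclusion.

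On size, the Sample size section states: "With an alpha risk of 0.05 and a potency of 80%, the sample size should be 170 patients/group, or 340 patients in all".

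**The concern.** The primary outcome is a past-month state at 6 months. The same state before randomisation is an obvious candidate predictor, and the trial's own 30-day drinking calendar (A-TLFB) can measure it. Entry criteria allow that state to vary: ages run from 14 to 17, one lifetime drink is enough, and the Background reports that half of French 17-year-olds had a binge in the previous month. Neither baseline drinking nor age is a stratification factor, so neither reaches the model through the strata.

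Leaving out a prognostic baseline covariate costs power in a logistic model and precision in a linear one. Reserve matters here. The plan expects 700 × 1/2 = 350 randomised against 340 needed, a slack of 10/350 = 2.9%, and the Strengths and limitations section itself anticipates attrition. The trial is also open-label with a self-reported outcome, so a baseline covariate added after the data are seen would be open to challenge. It needs to be named in advance.

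**Working it through.** **1. Reproduce the stated sample size.** Inputs from the Sample size section: control 50% ("50% of adolescents who have had at least one binge-drinking episode in the last month are expected in the control arm"), intervention 35% ("35% are expected in the intervention group"), alpha 0.05, power 80%. Sidedness is not stated.

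Two-sided test of two proportions, pooled variance under the null, no continuity correction, mean rate 0.425:

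n = [1.960 × √(2 × 0.425 × 0.575) + 0.842 × √(0.50 × 0.50 + 0.35 × 0.65)]² / 0.15²

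= [1.370 + 0.582]² / 0.0225 ≈ 169.3, rounded up to **170 per group**.

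This matches exactly, and power at 170 per group is 80.2%. Variants do not match: unpooled 167, continuity-corrected 183, one-sided 134. The figure is therefore two-sided and assumes no gain from covariates.

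**2. Simulate the primary model with and without baseline binge status.** Inputs not in the documents, and so assumed: baseline binge prevalence π of 30% or 50%, and a conditional odds ratio between baseline and 6-month binge status (OR) of 1 to 20. Trait and recruitment route were assumed to have no effect on the outcome. Age was not simulated.

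For each scenario the intercept a and treatment effect t were solved so that the marginal rates stay at the planned values, with expit(x) = 1/(1 + e^−x):

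- π·expit(a + ln OR) + (1 − π)·expit(a) = 0.50
- π·expit(a + t + ln OR) + (1 − π)·expit(a + t) = 0.35

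Example, π = 50% and OR = 6: control-arm risk is 0.29 without and 0.71 with a baseline binge (mean 0.50), and the conditional treatment odds ratio is 0.475.

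There were 4,000 trials per scenario, 170 per arm, analysed by Wald test at two-sided 0.05. Simulation error of each power is about √(0.8 × 0.2/4000) = 0.6 points.

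| OR | Power, π = 50%: strata only / plus baseline | Gain (points) | Power, π = 30%: strata only / plus baseline | Gain (points) |
|---|---|---|---|---|
| 1 | 78.9% / 78.5% | −0.4 | 80.2% / 80.2% | 0 |
| 2 | 81.0% / 81.8% | 0.9 | 79.2% / 80.3% | 1.1 |
| 4 | 79.8% / 84.1% | 4.3 | 79.4% / 83.4% | 3.9 |
| 6 | 81.0% / 87.2% | 6.2 | 80.1% / 86.1% | 6.0 |
| 10 | 79.9% / 90.0% | 10.1 | 79.5% / 88.7% | 9.3 |
| 20 | 80.9% / 94.7% | 13.8 | 79.8% / 91.8% | 12.0 |

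Gains are taken from the unrounded powers. Type I error (π = 50%, OR = 10) is 5.2% without and 5.1% with the covariate.

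**3. Effect on the reported estimate.** The marginal odds ratio for 35% against 50% is (0.35/0.65)/(0.50/0.50) = 0.54. At OR = 10 the conditional odds ratio behind the same marginal rates is 0.44 (π = 50%) or 0.45 (π = 30%). The two answer different questions, so the report has to say which is shown.

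**4. How much reserve there is.** No rate of missing primary outcomes is given. If a share of the 170 per arm is missing, power without a baseline covariate is 75.9% at 10% (153 per arm), 70.8% at 20% (136) and 65.0% at 30% (119). The adjusted model was not simulated under attrition.

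**The case against.** The best defence is that nothing here is wrong. Adjusting for the stratification factors matches the stratified randomisation, the stated number is exact, the test holds its level, and chance imbalance is already covered by the standard error. All of that stands.

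Second, this is a journal article. An analysis plan that is not shown may name further covariates, and the article does not say that the strata are the only ones. That is fair, but the article does fix a primary model and its adjustment set, and a plan written to that text would have no baseline drinking term.

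Third, the gain depends on an association that the documents do not give. At an odds ratio of 2 it is about 1 point. This also stands, and it limits what can be claimed.

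A reader might infer several stronger points that the documents do not support:

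- *The trial is underpowered because of this model.* It is not: the planned model delivers the planned 80% on complete data.
- *Baseline binge drinking is the strongest predictor of the outcome.* That is plausible, but no document says so or gives a baseline rate.
- *A claim of reduction requires starting status in the model.* The Study design section refers to the "program on the reduction of binge drinking episodes, over usual routine follow-up care". That is a between-group superiority claim, and the aim, main criterion and analysis all describe a comparison of prevalence, so there is no contradiction.
- *Every quantitative outcome ignores its baseline.* The covariates of the mixed model are not stated, so the point rests on the linear-model sentence alone.

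**Conclusion.** The point holds as a matter of forgone efficiency, not of validity or arithmetic. The named adjustment set omits baseline drinking in a sample whose entry criteria allow it to vary widely. Prespecifying it would leave type I error unchanged and lose nothing beyond simulation error if the covariate proved uninformative. It would add about 1 point of power at an odds ratio of 2, 4 at 4, 6 at 6, 9 to 10 at 10, and 12 to 14 at 20. These figures assume 170 evaluated per arm, marginal rates of 50% and 35%, and baseline prevalence of 30% or 50%; the odds ratios and the baseline prevalence are assumptions. For quantitative scales the direction is the same, but the documents give no baseline correlation from which to size the gain. With about 2.9% slack for missing outcomes, the change is worth making.

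**What to change.** - **Primary model.** Prespecify past-30-day binge status before randomisation (A-TLFB, yes/no) as a covariate alongside trait and recruitment route. Age may be added, but its contribution was not quantified here.
- **Other outcomes.** Include the baseline score of each quantitative scale in its linear model, and state how baseline enters the mixed model.
- **Reporting.** Label the adjusted odds ratio as conditional, and also report a standardised marginal prevalence difference so that the result stays on the planned 50% versus 35% scale.
- **Data.** Confirm that the A-TLFB is completed before randomisation. The text lists assessments only at 1, 3, 6 and 12 months after the intervention and the design figure was not available, so a baseline calendar is likely but not confirmed.

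Cost: a few lines of model specification, slightly more analysis work for the standardisation and, if not already scheduled, one 30-day calendar at the inclusion visit. The sample size need not change.

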### Harms

The study may be stopped prematurely in the event of unexpected, serious adverse events requiring a review of the strategy. Unexpected or serious events will be collected by investigators.

### Data management and confidentiality

Data entry will be carried out on an electronic medium via a web browser. Data analysis will be carried out by a biostatistician from the Data Management Unit (CHRU BREST) under the responsibility of [name].

Persons with direct access will take all necessary precautions to ensure the confidentiality of information relating to the products, the tests, the persons who take part in them and in particular with regard to their identity and the results obtained. These persons, in the same way as the investigators themselves, are subject to professional secrecy (according to the conditions defined by articles 226–13 and 226–14 of the French penal code).

During the research or at its end, the data collected on the persons who are subject to such secrecy and transmitted to the sponsor by the investigators (or any other specialized contributors) will be made anonymous. Under no circumstances should the names or addresses of the persons concerned be made clear. Only the first letter of the subject’s surname and the first letter of the subject’s first name will be recorded, accompanied by a coded number specific to the study indicating the order of inclusion of the subjects. The sponsor will ensure that each person involved in the research has given written consent for access to individual data concerning him or her that is strictly necessary for the quality control of the research.

